### Aim and research questions

Therefore, given the potential benefits of physical exercise and the possibilities of optimizing how it is prescribed for cancer patients, the current randomized controlled trial aims to analyze the effectiveness of a high-intensity remote exercise program guided daily by HRV compared to a pre-planned remote moderate to high-intensity exercise program in breast cancer survivors. For this purpose, the effects of both physical exercise programs on physiological (cardiotoxicity, inflammatory factors, cardiovascular variables, body composition and anthropometric parameters), physical (low and upper body strength, cardiorespiratory fitness, low and upper body flexibility, agility and balance) and psychological health (HRQoL, fatigue, life satisfaction, self-esteem, anxiety and depression, shoulder disability perception, physical activity, kinesophobia and exercise motivation) measurements of breast cancer patients will be assessed and compared an inactive control group.

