#### Sample size

Given that, to our knowledge, no previous studies have examined the effects of an exercise program guided by daily HRV in breast cancer patients and its comparison to a moderate to high-intensity exercise group and a control group, the sample size was calculated by considering the exercise intensity differences between groups. In this regard, we have taken as reference values interventions carried out with three groups, a high-intensity group, a moderate-intensity group and a control group. Moreover, the oxygen consumption peak (VO_2peak_) has been selected to make the calculations due to its importance in cardiovascular and physical health. The chosen tool to analyze sample size has been using G-Power 3.1 and the calculation were done basing us on the data from the investigations carried out by Martin, Battaglini [46] and Northey, Pumpa [47] two different studies. In both cases, between-group significant differences were reported.

A total of 18 patients, (11 allocated to the experimental and 11 allocated to the control group) would be needed in the worst of the cases to achieve a 99% statistical power for VO_2peak_. Moreover, regarding the low number of participants obtain, the calculations concerning the effects of exercise in Global Longitudinal Strain (GLS) compared to a control group were also done. In this case, the data employed for the calculation was from Costello, Roberts [48] where significant differences within and between groups were achieved. So, in the prior calculations performed, we would need a total of 50 patients [25 in each group] to achieve a 99% statistical power (two tails). Therefore, assuming 20% of dropouts, 90 patients will be recruited and allocated to one group or the other. Due to the large number of patients that are estimable to be enrolled in the study, the recruitment and intervention will be carried out progressively over 24 months depending on the number of patients to be recruited.

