### Statistical analysis

All the outcome results will be included in an anonymous database to conduct the statistical analyses. A descriptive, quantitative, and graphics analysis will be performed of all the included variables. The statistic software employed will be the IBM Statistical Package for the Social Sciences (version 25.0; SPSS, Inc., Chicago, IL, USA) [115]. The number of statistical analyses will be high and diverse depending on the nature of the results. In general, we will proceed with the usual steps to check the normality and homogeneity of variables.

First, the Kolmogorov–Smirnov and Shapiro Wilk tests will be used to determine whether parametric or non-parametric statistical analyses should be applied to each of the variables analyzed. In this regard, normal distribution will be assumed when the p-value is greater than 0.05 indicating that the variable tested was not significantly different from a normal distribution. Descriptive results will be presented as mean and SD or median (range) according to the results of the normality tests. Subsequently, to evaluate the effects of the program, a repeated-measures ANOVA or Kruskal–Wallis, depending on the normal distribution, will be used. The interaction factors of the ANOVA, or Kruskal–Wallis, will be the group (HRVG, PEG or CG) and the timing of the measure (before, after the intervention and follow-up). Besides, a Bonferroni analysis will be performed to adjust the results. Results shall include the Cohen’s d effect size (95% confidence interval) and statistical significance for each dependent variable concerning time and its interaction effects (group × time). Moreover, to analyze the differences between the group independently in each of the variables, the T-test for Independent Samples and the T-test for related samples, or a Mann–Whitney U-test or Wilcoxon in case of not fulfilling the principle of normality, will be employed.

Concurrently, a correlation analysis is planned to be done to establish novel relations between some of the measures performed. For instance, a Pearson o Spearman analysis (depending on the results of the normal distribution analysis) will be calculated between the change in strength, the body composition, cardiotoxicity variables and the psychological variables. Moreover, a correlation between the results obtained in the different questionnaires will be calculated.

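### Bonferroni is named without its family; for the three pairwise group contrasts it is valid but needlessly conservative, since Holm keeps the same family-wise error and never rejects less

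*Protocol article*

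**What the plan says.** The protocol article, Statistical analysis, plans a repeated-measures ANOVA or a Kruskal–Wallis test for each outcome. The factors are "the group (HRVG, PEG or CG) and the timing of the measure (before, after the intervention and follow-up"). The next sentence is the only one on multiplicity: "Besides, a Bonferroni analysis will be performed to adjust the results". It does not say whether the adjustment covers pairs of groups, time points, outcomes or some combination, and it gives no adjusted threshold.

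The same paragraph then adds further tests: "to analyze the differences between the group independently in each of the variables, the T-test for Independent Samples and the T-test for related samples", or Mann–Whitney and Wilcoxon tests where normality fails. No adjustment is attached to these.

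No significance level is stated for the treatment comparisons. The value 0.05 appears only for the normality check ("normal distribution will be assumed when the p-value is greater than 0.05").

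Under Aim and research questions, the leading comparison is between the two exercise groups: "analyze the effectiveness of a high-intensity remote exercise program guided daily by HRV compared to a pre-planned remote moderate to high-intensity exercise program". Comparison with the control group is named as well.

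**The concern.** With three arms there are three group pairs. If Bonferroni covers those pairs at a family-wise 0.05, each is tested at 0.05/3 = 0.0167, whatever happens to the other two. HRVG versus PEG leads the aims and may well be the smallest of the three differences. HRVG patients train at PEG intensity on any day their HRV falls outside their limits, and the Discussion cites two meta-analyses that found no added gain from high over moderate intensity. The Sample size section bases its echocardiographic calculation on exercise versus control ("we would need a total of 50 patients [25 in each group] to achieve a 99% statistical power (two tails")), not on this pair. A method that costs power for no gain in error control therefore bears most on the comparison with least power to spare.

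**Working it through.** **Inputs**

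- Arms: 3, hence 3 pairwise contrasts (Statistical analysis).
- The plan's own figure: 25 per group × 3 = 75, and 75 × 1.2 = 90, which reproduces the stated total.
- Patients per arm at analysis: 90 × 0.8 / 3 = 24. Equal allocation is an assumption, because no ratio is stated.
- Family-wise level: 0.05 two-sided, assumed.
- Arm means in SD units: assumed over a range, because the document gives no effect size for HRVG versus PEG. One anchor is available. A figure of 25 per group at 99% power, two-sided 0.05, implies d of about 1.24 for exercise versus control (two-sample t-test).

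**Why Holm cannot do worse.** Order the three p-values. Bonferroni compares each with 0.05/3. Holm compares the smallest with 0.05/3, the next with 0.05/2 and the largest with 0.05, and stops at the first failure. Every threshold is at least 0.05/3, so any contrast that Bonferroni rejects is also rejected by Holm. Both hold the family-wise error at 5% or less for any valid p-values, so the argument also covers Mann–Whitney tests. It holds for a family of any size.

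**Limits of the gain, by formula.** With pooled variance on 3 × (24 − 1) = 69 degrees of freedom, the noncentrality for a difference of δ SDs is δ × √(24/2). For δ = 0.5 this is 0.5 × 3.464 = 1.732.

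- Bonferroni: critical t = 2.454, power 24.3%.
- No adjustment: critical t = 1.995, power 40.1%.

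Holm must lie between these two, so its gain at δ = 0.5 cannot exceed 40.1 − 24.3 = 15.8 points. Where it falls depends on how often the two contrasts with control are rejected first.

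**Simulation** (400,000 runs per row, one time point, 24 per arm, SD 1). Power for HRVG versus PEG:

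| Means HRVG / PEG / CG | Bonferroni | Holm | Gain (points) |
|---|---|---|---|
| 0.5 / 0.25 / 0 | 6.1% | 7.4% | 1.3 |
| 0.5 / 0 / 0 | 24.2% | 26.0% | 1.8 |
| 0.8 / 0.5 / 0 | 8.5% | 11.7% | 3.2 |
| 0.8 / 0.3 / 0 | 24.4% | 28.9% | 4.5 |
| 1.0 / 0.5 / 0 | 24.2% | 31.2% | 7.0 |
| 1.2 / 0.6 / 0 | 36.1% | 46.6% | 10.5 |
| 1.24 / 0.74 / 0 | 24.3% | 35.1% | 10.8 |
| 1.74 / 1.24 / 0 | 24.3% | 39.9% | 15.6 |

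**Family-wise error.** With all three arms equal it is 4.4% for both methods (12.2% with no adjustment). With HRVG and PEG equal and both 1.2 SD above control, the only true null is HRVG versus PEG. It is then rejected in 1.7% of runs by Bonferroni and 4.6% by Holm. Both are within 5%, but Bonferroni uses only about a third of the allowance.

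**The case against.** The strongest reply is that Bonferroni is a valid and common choice, so an alternative with more power is only a preference. The first half stands: nothing becomes invalid if the sentence is left as it is, and the protocol sets no power target for HRVG versus PEG that Bonferroni causes it to miss. The second half does not. Holm is at least as good in every case at the same error level, so for the tests themselves there is nothing to weigh against it.

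A second reply is that the text does not tie Bonferroni to the group pairs. This also stands in part. Group pairs are the natural reading, because the sentence directly follows an ANOVA with a three-level group factor, but time is a factor in the same ANOVA. A reader might infer that HRVG versus PEG is fixed at a 0.0167 threshold. The document does not state that figure, and the follow-on two-sample tests could be read as unadjusted. The missing family is therefore part of the point.

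A third reply is that Bonferroni has matching simultaneous confidence intervals and is available in the SPSS menu, while Holm has no simple intervals of that kind. This is a real cost and is carried into the fix.

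Two stronger readings should be resisted. One is that the power gain is large in general. The table shows that for Holm it is not: the gain is large only when exercise beats control by a wide margin. The other is that the closed three-arm procedure (an overall F test, then unadjusted pairs) is the obvious replacement because it gains more, for example 39.5% power at 1.0 / 0.5 / 0. It does not strictly dominate Bonferroni. With the third mean midway, F = t²/2. A pair with t between 2.454 and 2.502 then passes Bonferroni while F, at 3.01 to 3.13, falls short of its critical value of 3.13. Nor does the planned group-by-time ANOVA supply the overall test that this procedure needs.

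**Conclusion.** The point holds as a modest, inexpensive improvement and not as an error. That Holm never rejects less over the same family is certain and needs no assumption. The size of the gain for HRVG versus PEG is conditional on the assumed means, 24 per arm, a family-wise two-sided 0.05 and a single-time-point comparison with equal SDs; the repeated-measures model itself was not simulated. Under these assumptions the gain is about 1 to 3 points for modest effects over control, and about 7 to 16 points once HRVG exceeds control by an SD or more. A reader might infer that Bonferroni is why the leading question is underpowered. The figures do not support that: in the scenarios tabulated, Holm still leaves power between about 7% and 47%.

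**What to change.** Replace the Bonferroni sentence with one that names the family and the method: for each outcome, the three pairwise group contrasts (HRVG–PEG, HRVG–CG, PEG–CG), including those obtained from the follow-on independent-samples t-tests or Mann–Whitney tests, form one family and are adjusted by Holm. If several post-baseline time points are tested, the same sentence should say whether each has its own family of three. Baseline adjustment and the choice of a single leading visit are separate decisions, and this change does not require them.

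The cost is small. Holm p-values need a short hand calculation outside the SPSS menu: multiply the ordered p-values by 3, 2 and 1, do not let any adjusted value fall below the one before it, and cap at 1. Because there are no simple matching simultaneous intervals, the 95% confidence intervals would be unadjusted and must be labelled so, with a note that they can disagree with the adjusted p-values. No extra patients or measurements are needed.

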## Abstract

**Background:**

Breast cancer is a chronic disease with a large growth in its treatments, prognosis, improvements, side effects and rehabilitation therapies research. These advances have also highlighted the need to use physical exercise as a countermeasure to reduce the cardiotoxicity of pharmacological treatments, increase patients' strength and quality of life and improve body composition, physical condition and mental health. However, new investigations show the need for a closed exercise individualisation to produce higher physiological, physical and psychological benefits in remote exercise programs. To this end, the present study will use, in a novel way in this population, heart rate variability (HRV) as a measure for prescribing high-intensity training. Thus, the primary objective of this randomised clinical trial is to analyse the effects of a high-intensity exercise program daily guided by HRV, a preplanned moderate to high-intensity exercise intervention and a usual care group, in breast cancer patients after chemotherapy and radiotherapy treatments.

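### The reported group × time p-value covers three arms and four visits and cannot answer the HRVG-versus-PEG aim; the two-group tests that could are not tied to it or adjusted for baseline

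*Protocol article*

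**What the plan says.** Under Aim and research questions, the article sets out to analyse "the effectiveness of a high-intensity remote exercise program guided daily by HRV compared to a pre-planned remote moderate to high-intensity exercise program". The next sentence adds that the effects of both programmes "will be assessed and compared an inactive control group". The abstract is broader still: the "primary objective of this randomised clinical trial is to analyse the effects of a high-intensity exercise program daily guided by HRV", alongside the pre-planned programme and usual care.

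Under Statistical analysis, "to evaluate the effects of the program, a repeated-measures ANOVA or Kruskal–Wallis, depending on the normal distribution, will be used". Its factors "will be the group (HRVG, PEG or CG) and the timing of the measure (before, after the intervention and follow-up"). The Outcomes section fixes four assessments: before, after, and 3 and 6 months after the end of the intervention. The results to be reported are Cohen's d with a 95% confidence interval and "statistical significance for each dependent variable concerning time and its interaction effects (group × time").

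The same section adds two further elements. One is a multiplicity step: "Besides, a Bonferroni analysis will be performed to adjust the results". The other is a set of independent-samples and paired t-tests, or Mann–Whitney and Wilcoxon tests, for differences between groups. It does not say which of these answers the HRVG-versus-PEG question, and no baseline adjustment is described.

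**The concern.** The analysis named for programme effects tests one thing and the aim asks another. The interaction is significant whenever any arm's profile departs from any other's at any visit. It is therefore expected to be significant if both exercise programmes beat usual care equally, which would say nothing about whether HRV guidance adds to a pre-planned programme.

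Cohen's d has a related problem. It is a standardised difference between two means, so it is not defined for an interaction on 6 degrees of freedom, and the sentence promising it cannot be carried out as written.

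At stake is the interpretation of the trial's novel element. The p-value the plan puts forward is silent on it, and the two-group test that does address it is less precise than the collected data allow.

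**Working it through.** **Inputs from the article.** Three arms; four visits; 25 per group from the global longitudinal strain calculation; 20% dropout; 90 patients in total.

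**Assumed, because not given.** Equal allocation, two-sided alpha 0.05 for efficacy, equal within-patient correlation r of 0.5 or 0.7, and effects in SD units of a single visit. The effect either fades (profile 0, 1, 0.5, 0.5 over the four visits) or is held (0, 1, 1, 1).

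**Sample size.** 3 × 25 = 75, and 75 × 1.2 = 90, which matches the article. With 20% lost, 90 × 0.8 = 72, or 24 per arm.

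**Degrees of freedom.** Interaction: (3 − 1)(4 − 1) = 6. Error: 3 × (24 − 1) × (4 − 1) = 207.

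**Group × time when HRVG = PEG and both exceed control by δ.** The noncentrality is λ = n × (2/3) × S × δ² / (1 − r). Here 2/3 is the sum of squares of the centred group pattern (1, 1, 0), and S is the sum of squares of the centred time profile: 0.5 for fading, 0.75 for held. Example: 24 × (2/3) × 0.5 × 0.25 / 0.5 = 4.0.

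| δ (SD) | r | Profile | λ | P(significant) |
|---|---|---|---|---|
| 0.5 | 0.5 | fading | 4.0 | 26% |
| 0.5 | 0.5 | held | 6.0 | 39% |
| 0.5 | 0.7 | fading | 6.7 | 43% |
| 0.5 | 0.7 | held | 10.0 | 63% |
| 0.8 | 0.5 | fading | 10.2 | 64% |
| 0.8 | 0.5 | held | 15.4 | 84% |
| 0.8 | 0.7 | fading | 17.1 | 88% |
| 0.8 | 0.7 | held | 25.6 | 98% |

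With no effect in any arm, the rate is 5%.

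**The same rates arise when only HRVG works.** The pattern (1, 0, 0) also has centred sum of squares 2/3, so every λ above is unchanged if HRVG alone beats PEG and control. The p-value cannot tell the two situations apart.

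**The planned t-test when HRVG = PEG.** In 20,000 simulated trials per scenario, an HRVG–PEG t-test at the post-intervention visit rejected in 4.7% to 5.1%. Requiring a significant interaction as well gave about 2% to 5%; adding Bonferroni over three pairs gave about 0.7% to 1.7%.

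**Power for a 0.5 SD HRVG–PEG difference at the post-intervention visit.**
- Unadjusted t-test: noncentrality 0.5 / √(2/24) = 1.73 on 46 df.
- Baseline-adjusted contrast from a three-arm ANCOVA: 0.5 / √(2(1 − r²)/24) = 2.00 at r = 0.5 and 2.43 at r = 0.7, on 72 − 4 = 68 df.

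| Test | Alpha 0.05 | Alpha 0.05/3 |
|---|---|---|
| Unadjusted t-test | 40% | 24% |
| ANCOVA, r = 0.5 | 50% | 33% |
| ANCOVA, r = 0.7 | 67% | 49% |

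If the t-test were run on change scores, the noncentrality would be 0.5 / √(4(1 − r)/24): 1.73 at r = 0.5 (40%) and 2.24 at r = 0.7 (59%).

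**Against the interaction test, with PEG equal to control.**

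| r | Profile | Group × time | ANCOVA, 0.05 | ANCOVA, 0.05/3 |
|---|---|---|---|---|
| 0.5 | fading | 26% | 50% | 33% |
| 0.5 | held | 39% | 50% | 33% |
| 0.7 | fading | 43% | 67% | 49% |
| 0.7 | held | 63% | 67% | 49% |

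With PEG halfway between control and HRVG (0.5 SD steps, fading, r = 0.5), the interaction rejects in 72%, largely because exercise differs from control.

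**The case against.** Four stronger readings are tempting, and the article does not support them.

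- **That the plan has an inflated error rate.** In the 26% to 98% scenarios the interaction null is false, so rejecting it is right. Nothing in the article says that a significant interaction will be presented as proof of HRV guidance.
- **That HRVG is never compared with PEG.** Independent-samples tests are planned, and in a three-arm trial these are pairwise. A Bonferroni step is stated too.
- **That the interaction test loses power whenever the exercise arms differ.** It does so when PEG is close to control and the effect fades. With a held effect the gap is smaller, and at 0.05/3 it shrinks to 6 or 7 points (fading) or reverses (held). With control well below both arms, the interaction rejects more often than the contrast.
- **That the Bonferroni comparisons would be made on arm means averaged over all visits, baseline included.** The article does not say so.

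It is also fair that the aim and the abstract's objective include the control group, which a three-arm test partly addresses. The Cohen's d sentence may be loose wording for effect sizes on the two-group comparisons. The detail of contrasts may also sit in a fuller analysis plan.

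What stands is what the article does fix: the test for programme effects, its factors and the p-values to be reported. Those do not match the first-stated aim, and the two-group tests are specified without baseline adjustment.

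**Conclusion.** The point holds in a limited form. The group × time result cannot by itself support or refute a benefit of HRV-guided over pre-planned exercise. It has the same chance of significance whether both programmes work equally or only the HRV-guided one works: about 26% to 98% for effects of 0.5 to 0.8 SD. This is a mismatch between test and question, not a type I error problem.

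The firm gain from changing the plan is in precision over the unadjusted t-test: 40% to 50% power at r = 0.5 and 40% to 67% at r = 0.7 for a 0.5 SD difference; with Bonferroni over three contrasts, 24% to 33% and 24% to 49%. If the t-test were intended on change scores, the gain at r = 0.7 and alpha 0.05 would be 59% to 67%. Any advantage over the interaction test is conditional and should not be the argument for the change.

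All figures rest on 24 per arm, equal allocation, alpha 0.05 and the assumed correlations and effect sizes. The mismatch itself depends on none of them.

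**What to change.** In the Statistical analysis section:

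1. Name the HRVG–PEG difference at the post-intervention visit, adjusted for the baseline value by ANCOVA and given with a 95% confidence interval, as the test of the stated HRVG-versus-PEG aim. It replaces the unadjusted t-test for that comparison.
2. Give HRVG–CG and PEG–CG in the same way, and apply the Bonferroni step to these three contrasts.
3. Report Cohen's d for each contrast rather than for the interaction.
4. State that a significant group × time result alone does not support a claim about HRV guidance.

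This changes wording only; no additional patients, visits or measurements are needed. The cost is that the lead contrast is tied to one visit, so differences at 3 and 6 months become secondary for it. Even after the change, power for a 0.5 SD difference between the exercise arms stays modest.

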**Methods:**

For this purpose, a 16-week intervention will be carried out with 90 breast cancer patients distributed in 3 groups (a control group, a moderate to high-intensity preplanned exercise group and a high-intensity exercise group guided by HRV). Both physical exercise interventions will be developed remotely and supervised including strength and cardiovascular exercises. Physiological variables, such as cardiotoxicity, biomarkers, lipid profile, glucose, heart rate and blood pressure; physical measures like cardiorespiratory capacity, strength, flexibility, agility, balance and body composition; and psychosocial variables, as health-related quality of life, fatigue, functionality, self-esteem, movement fear, physical exercise level, anxiety and depression will be measure before, after the intervention and 3 and 6 months follow up.

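### Planned correlations between outcome changes state no adjustment for randomised arm; if the arms are pooled, two changes that both respond to exercise can appear related

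*Protocol article*

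**What the plan says.** The last paragraph of Statistical analysis in the protocol article sets out a correlation analysis, separate from the analysis of programme effects. Its purpose is given as "a correlation analysis is planned to be done to establish novel relations between some of the measures performed". As an example, a Pearson or Spearman coefficient, chosen by the normality tests, "will be calculated between the change in strength, the body composition, cardiotoxicity variables and the psychological variables". In addition, "a correlation between the results obtained in the different questionnaires will be calculated", with no time point given.

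The same section brings in arm for the main analysis: the factors of the ANOVA or Kruskal–Wallis "will be the group (HRVG, PEG or CG) and the timing of the measure". The independent-samples tests also compare groups. For the correlations, the article gives the coefficient, the rule for choosing it and the families of variables. It mentions no arm term, partial correlation or within-arm calculation.

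**The concern.** The trial has two exercise arms and one usual-care arm, and it expects exercise to move the same families of variables that it plans to correlate. Suppose all patients are put into one correlation. Those in the exercise arms then tend to have larger changes in both variables, and those in usual care smaller changes in both. That alone gives a non-zero coefficient, even if patients who gain more strength than others in their arm do no better on the second measure. The coefficient then partly restates the treatment effect and would be read as a link between two measures.

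The normality checks and the Bonferroni step do not deal with this, because the problem is neither distributional shape nor multiplicity. What is at stake is the reading of the exploratory results, for example an apparent link between strength gain and a cardiotoxicity marker. The bias grows with the effect of exercise on the two variables.

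**Working it through.** The article gives no figure for the correlations, so there is none to reproduce. The check asks how large the induced correlation is and how often it would reach significance.

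**Inputs**
- Patients: the Sample size section recruits 90 and allows 20% dropout ("assuming 20% of dropouts, 90 patients will be recruited and allocated to one group or the other"). 90 × 0.80 = 72 completers.
- Arms: three (Abstract, Methods). No allocation ratio is stated. Equal arms are assumed, so 72 / 3 = 24 per arm.
- Level: none is stated for the correlations. Two-sided 0.05 is assumed.
- Effect size: the calculation for global longitudinal strain (GLS) is "a total of 50 patients [25 in each group] to achieve a 99% statistical power (two tails". At an assumed two-sided 0.05, the noncentral t distribution gives 99% power with 25 per group at d = 1.24. The article gives no effect size or SD, so this is back-calculated.
- Truth assumed: zero correlation within every arm, within-arm SD of 1, and both exercise arms shifted against control by d₁ on one variable and d₂ on the other.

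**Formula.** With two thirds of patients exercising, the between-arm variance of the exercise indicator is (2/3)(1/3) = 2/9. Hence

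r = (2/9)d₁d₂ / √[(1 + (2/9)d₁²)(1 + (2/9)d₂²)].

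For equal effects this reduces to (2/9)d² / (1 + (2/9)d²). Examples:
- d = 0.5 in both: 0.0556 / 1.0556 = 0.05.
- d = 1.24 in both: 0.3417 / 1.3417 = 0.25.
- d = 1.24 and 0.5: 0.1378 / √(1.3417 × 1.0556) = 0.1378 / 1.190 = 0.12.

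**Rejection rates.** Simulation, 20,000 trials per row, pooled Pearson, N = 72:

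| d₁ | d₂ | induced r | pooled, p < 0.05 | adjusted for arm |
|---|---|---|---|---|
| 0.2 | 0.2 | 0.01 | 5% | 5% |
| 0.5 | 0.5 | 0.05 | 7% | 5% |
| 0.8 | 0.8 | 0.12 | 18% | 5% |
| 1.0 | 1.0 | 0.18 | 34% | 5% |
| 1.24 | 1.24 | 0.25 | 61% | 5% |
| 1.24 | 0.5 | 0.12 | 16% | 5% |
| 1.24 | 0.3 | 0.07 | 9% | 5% |
| 1.24 | 0.2 | 0.05 | 7% | 5% |

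In the equal-effect rows Spearman is within about one percentage point of Pearson. With no dropout (N = 90, 30 per arm) the pooled rates are somewhat higher, for example 22% at d = 0.8 in both and 70% at d = 1.24 in both. The induced r depends on the product of the two effects, so a large effect on one variable does little unless the other also responds. The sign of r follows the directions of the two effects.

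**The case against.** The strongest reply is that the article never says the arms are pooled. Its example is illustrative, separate correlations within each arm would fit the text, and a full protocol or analysis plan may settle the matter. This stands to the extent that pooling is an inference. It is still the plain reading: the section names arm where arm is meant to enter, and for the correlations it names only methods that take two variables and nothing else.

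A second reply concerns size. A reader might infer that unrelated outcomes will generally appear related. The table does not support that: at modest effects the rate is close to nominal, and even at d = 1.0 in both variables a false signal is less likely than not. The 61% applies the GLS effect to both variables, and the article implies no such effect for strength, body composition or psychological scores.

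A third reply is that pooled and within-arm correlations answer different questions, so a non-zero pooled value is not wrong in itself. That is fair, but a relation between two measures, which is the stated purpose, is a claim beyond each of them responding to exercise. The within-arm quantity bears on that claim.

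Finally, questionnaire scores correlated at baseline are not exposed, since no intervention has yet taken place. That stands, and the fix is limited accordingly.

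**Conclusion.** The concern holds in a limited form. No adjustment for arm is stated, and if the arms are pooled the coefficients mix the treatment effect with the association between measures. Under the assumptions listed, the chance of a false relation runs from about nominal when either effect is small to about 61% when both variables carry the effect implied for GLS. Adjustment returns it to about 5% in every case.

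A reader might go further and conclude that the trial's conclusions are at risk, or that false mechanisms will be reported. The documents do not support that. The stated aims are comparisons between groups, the correlations are exploratory, the text does not speak of mediation, and the main group comparison is untouched.

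**What to change.** Add one sentence to Statistical analysis: correlations between changes, and between questionnaire scores measured after baseline, will be calculated as partial correlations adjusted for randomised arm (Pearson or rank-based; equivalently, pooled within-arm), with any unadjusted pooled value shown only as a supplement.

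The cost is two degrees of freedom (70 to 68 with 72 completers). It needs no additional data. If a within-arm analysis was already intended, the same sentence removes the ambiguity.
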